**RATIONALE**

*S. pneumoniae* is frequently isolated from nasal swabs of healthy subjects, but it can also cause severe diseases (pneumonia, bacteraemia, meningitis and sepsis).HIV-infected subjects are more sensitive to invasive diseases and recurrent infection than the general population. Nasal carriage is the main pathogenetic feature for invasive disease: bacteraemia is more frequent in carriers, HIV+ patients are constantly colonized by the same pneumococcal strain and their nasopharyngeal isolates have features similar to subsequent invasive strains. A 23-valent polysaccharide vaccine (PPV23) has long been available and recommended in the HIV+ population as prophylaxis for invasive disease. Studies regarding efficacy of PPV23 in HIV+ are controversial and highlight that immune response induced by PPV23 in HIV+ is poor and an hyporesponsiveness to repeated polysaccaridic antigens stimulation can occur. Moreover, PPV23 seems not to affect pneumococcal carriage status and could lead to emergence of non-vaccine serotypes. The conjugation of pneumococcal capsular polysaccharides to carrier proteins results in an improved T-cell dependent immune response, characterized by increased antibody concentrations and induction of T and B memory cells, with a demonstrated higher efficacy in children. A heptavalent vaccine conjugated with diphtheria toxoid (PCV7) is approved in Europe since 2001 and is effective in reducing incidence of invasive disease by vaccine serotypes (4, 6B, 9V, 14, 18C, 19F, 23F), in both children and adults, due to effect of herd immunity. A PCV13 formulation has recently been developed, covering PCV7 serotypes plus 1, 3, 5, 6A, 7F and 19A. PCV13 revealed the same safety profile as PCV7 in pediatric patients, that are the main target of conjugate vaccines licensure. Some trials showed a better antibody response in terms of quantity and quality in HIV + adults by using PCV7 as compared to PPV23. However these data were not unequivocally confirmed in further studies on the use of PCV7 alone or in combination with PPV23. The first trials of PCV13 use in adults showed the same or even better response compared to PPV23, with a safety and tolerability similar to PCV7. PCV13 in HIV+ adults is a promising candidate prophylactic measure for pneumococcal infections.

The purpose of this study is to evaluate serological response and prevalence of nasopharyngeal colonization by *S. pneumoniae* in HIV+ non-hospitalized adults, following vaccination with 2 doses of PCV13.

**Biological: pneumococcal conjugate 13 valent vaccine**

Pneumococcal polysaccharide conjugate vaccine(13-valent adsorbed) conjugated to CRM197 carrier protein and adsorbed on aluminum phosphate (0.125 mg of aluminum). Prevenar 13 is administered in two doses, each of 0.5 ml, with an interval of 2 months, injected intramuscularly in the deltoid muscle of the arm.

**Pharmaceutical form**: suspension for injection. Dosage: 0.5 ml, containing 2.2 g of polysaccharide for serotypes 1, 3, 4, 5, 6A, 7F, 9V, 14, 18C, 19A, 19F, 23F, and 4.4 micrograms for serotype 6B.

**Primary Outcome Measures:**

- Define the serological response after 2 doses of PCV13 vaccine. Measure of serological response after 2 doses of PCV13 vaccine (booster dose after 8 weeks) in HIV+ adults.
- Determine the rate of nasopharyngeal colonization by different pneumococcal serotypes in HIV-positive adults, in relation to baseline antibody titers at T0

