**Sample size and study group selection**

Applying these criteria, 50 HIV-infected adult outpatients who had never been vaccinated with any pneumococcal vaccine will be prospectively enrolled at two Infectious Diseases Clinical Centers in Central Italy (University Division of Infectious Diseases in Siena and Institute of Clinical Infectious Diseases, Catholic University of the Sacred Heart in Rome). All subjects will be required to sign a written informed consent before enrolling in the study.

At baseline (day 0, time of first vaccine dose administration), demographic, clinical and laboratory characteristics will be collected by patients interview.

At baseline, the enrolled patients will received two doses of the 13-valent vaccine (PCV13 Prevenar13®, Wyeth Vaccines) eight weeks apart.

Follow-up visits will be scheduled at 8 (time of second PCV13 dose), 24 and 48 weeks. At baseline and at each visit clinical and anamnestic data from patients will be recorded; peripheral venous blood samples will be collected to assess humoral immune response against PCV13 serotype; nasopharyngeal swabs will be collected, in order to investigate the *S. pneumonia* presence. CD4+ T cell count and plasma HIV-RNA will be also monitored.

After each vaccine administration, short- (30 minutes), medium- (≤5 days) and long-term adverse reactions will be monitored.

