**Clinical follow-up**

Subjects will be considered colonized by S. pneumoniae with at least one positive nasopharingeal swab. Colonized patients will be followed for the next 12 months so to observe potential invasive infections. Potential simultaneous colonization by two or more serotypes will be highlighted through the analysis of isolated colonies.

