**STATISTIC ANALYSIS**

Clinical and anamnestic data collected at enrolment and at each follow-up visit, will be integrated with microbiological and serological results and correlation analyses will be performed.

Further statistical analyses will be carried out considering the results from this study and from the sub-study (protocol code PNEUMO-HIV 2011).

To evaluate the immunological response, the geometric mean concentrations of IgG (GMCs) at baseline, 4,8,24 e 48 week will be calculated. The GMCs will be compared by Student's' t Test (For Paired Samples). The quantitative variable will be tested for normal distribution and compared by

Mann-Whitney or Kruskal-Wallis test.

Differences in proportion will be determined by chi squared test or fischer exact test.

Regression or logistic analyses (univariate and multivariate) will asses the association with colonization, infection, antibiotic resistance, and an efficient immune response (e.g. ≥0.35μg/mL).

Analyses were performed using the SPSS software package (version 17.0 Chicago, IL).

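### The carriage-by-antibody primary outcome pools patients already colonized when the T0 titre was drawn with later acquisitions, so any IgG rise caused by carriage biases the association toward or past the null

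*Supplement*

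**What the plan says.** Main study, Primary Outcome Measures: the second of two primary outcomes is to "Determine the rate of nasopharyngeal colonization by different pneumococcal serotypes in HIV-positive adults, in relation to baseline antibody titers at T0". The titre is fixed at T0. The swab or swabs that count are not named.

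Main study, Clinical follow-up: "Subjects will be considered colonized by S. pneumoniae with at least one positive nasopharingeal swab". The T0 swab is not set apart.

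Main study, Sample size and study group selection: T0 is the day of vaccination ("At baseline (day 0, time of first vaccine dose administration"). At baseline and at every visit, "peripheral venous blood samples will be collected to assess humoral immune response against PCV13 serotype", and a nasopharyngeal swab is taken as well. "Follow-up visits will be scheduled at 8 (time of second PCV13 dose), 24 and 48 weeks".

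Main study, Rationale: "HIV+ patients are constantly colonized by the same pneumococcal strain".

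Main study, Statistic Analysis: unspecified correlation analyses, and "Regression or logistic analyses (univariate and multivariate) will asses the association with colonization" among other outcomes. No rule separates patients already carrying at T0, and no outcome of new serotype-specific acquisition is defined.

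The sub-study (PNEUMO-HIV 2011) repeats the outcome in HIV-positive and HIV-negative adults. Its HIV-negative group is sampled at baseline only.

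**The concern.** For a patient who acquires a serotype after T0, the T0 titre precedes the event. For a patient positive at T0 it does not: serum and swab are simultaneous, and on the Rationale's premise of persistent carriage the strain has probably been there for some time. If carriage raises IgG to the carried serotype, such patients show a titre already altered by the outcome.

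Two effects then act in opposite directions on one coefficient: low IgG may permit carriage, and carriage may raise IgG. Matching the titre to the carried serotype does not remove this, because that is the titre carriage would raise. At stake is a primary outcome that could show a weak, absent or inverted relation even where low pre-existing IgG does predispose to carriage.

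**Working it through.** The plan has no figure to reproduce: the 50 patients are given without a carriage rate, effect size, SD or power.

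**From the documents:** simultaneous T0 serum and swab; later swabs at weeks 8, 24 and 48; colonized means any positive swab; 50 patients.

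**Assumed, with ranges:** ln IgG before carriage is normal with SD s = 1; true odds ratio 0.6 per unit; carriage multiplies IgG to its own serotype by f, from 1 (no rise) to 3; a share w of all positives is already present at T0.

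**Approximation.** Write β = ln 0.6. For an uncommon outcome, the mean gap in true ln IgG between positives and negatives is about βs². Carriage adds ln f to the share w of positives, so the observed gap is βs² + w ln f. Dividing by s² = 1 gives the observed log odds ratio, hence

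observed OR ≈ 0.6 × f^w.

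| Fold rise f | w = 1 (all at T0) | w = 0.75 | w = 0.5 | w = 0.25 |
|---|---|---|---|---|
| 1 | 0.60 | 0.60 | 0.60 | 0.60 |
| 1.5 | 0.90 | 0.81 | 0.73 | 0.66 |
| 2 | 1.20 | 1.01 | 0.85 | 0.71 |
| 3 | 1.80 | 1.37 | 1.04 | 0.79 |

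The sign reverses when f exceeds (1/0.6)^(1/w): 1.67-fold at w = 1, and 1.67² = 2.8-fold at w = 0.5.

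**Simulation.**
- T0 swab only, about 5% carriage: 0.60, 0.89, 1.21 and 1.84 for f = 1, 1.5, 2 and 3, as the formula predicts.
- Any positive swab, with T0 carriage and later acquisition at equal rates of 5–20% (so about half of positives at T0): about 0.74, 0.85 and 1.06–1.09 for f = 1.5, 2 and 3. Repeat runs move the first two by 0.01–0.02. When exactly half of positives are at T0, the 3-fold figure falls to 1.01–1.04. It is best read as at or just past the null.

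**After separation.** With the outcome restricted to new detection among patients negative at T0, the fitted odds ratio is 0.60 whatever f is. The same check with other true values returned 0.49–0.51 for 0.5 and 0.68–0.71 for 0.7. Vaccination was not modelled.

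**Precision.** If 5%, 10% or 20% carry at T0 and the same share of the remainder acquire later, expected acquisitions are 50 × 0.95 × 0.05 = 2.4, 50 × 0.90 × 0.10 = 4.5 and 50 × 0.80 × 0.20 = 8. With E events the standard error of the log odds ratio is about 1/√E. Around 0.6, the 95% interval is 0.6 × exp(±1.96/√5) = 0.25 to 1.44 with 5 events, and 0.32 to 1.12 with 10.

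**The case against.** Four arguments stand against the point.

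1. *The plan describes an association and claims no protection.* This stands. A reader might infer that the sponsor will read the coefficient as antibody protecting against carriage, since the plan uses 0.35 µg/mL as a seroprotection cut-off and the sub-study's purpose links the correlation analyses to the choice of prophylaxis. Neither passage says so of this outcome. The fault is one of missing specification: the plan does not say which association is meant.

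2. *Only the titre is fixed at T0, so later positives are already in time order.* This also stands. It is why 0.9, 1.2 and 1.8 cannot be given as the bias of the outcome as written; they apply only if every positive is present at T0. Under the any-positive definition the bias is diluted, but it remains, because T0 carriers still count as events.

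3. *No passage says that carriage raises IgG.* Correct. With no rise there is no bias, as the first row of the table shows.

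4. *Time-ordering brings its own problems.* Titres at day 0 and week 8 are drawn at vaccination visits, so they are not the titres in force during the following interval. Acquisitions will be few. Both are true, and they limit what the repair can claim. They do not justify mixing two kinds of positive in one outcome.

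**Conclusion.** The point holds as a defect of definition. One primary outcome combines existing and newly acquired carriage and relates both to a titre that precedes only the second. Under the assumptions above, with about half of positives present at T0, a true odds ratio of 0.6 would appear as about 0.74, 0.85 and 1.06–1.09 for 1.5-, 2- and 3-fold rises. Greater persistence moves these toward 0.9, 1.2 and 1.8. The size of the rise, the T0 share and the true odds ratio are all assumed.

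Two stronger conclusions are tempting and not supported. The first is that the sign will reverse: with half of positives at T0 this needs nearly a 3-fold rise, and the documents give no rise at all. The second is that the data cannot tell the two directions apart: in the main study the planned follow-up swabs and serotyping allow it, and only the plan's definition fails to use them. In the sub-study's HIV-negative group, with a single visit, they cannot be separated.

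**What to change.** In the main study's Primary Outcome Measures and Statistic Analysis, replace the single outcome by two:

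- **(a)** Carriage at T0 against T0 titre, reported as a cross-sectional description and not read as protection or susceptibility.
- **(b)** First detection of a PCV13 serotype at weeks 8, 24 or 48 among patients negative for that serotype at T0, against T0 log IgG to that serotype, pooled over serotypes with the patient as cluster.

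State beside (b) that events will be few and the interval wide. State also that vaccination at day 0 and week 8 changes the titre in force at later swabs, so (b) concerns the pre-vaccination titre only. Relating each visit's titre to the next swab would not avoid this, since two of the three intervals start at a vaccination visit.

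In the sub-study, specify only (a) for the HIV-negative group.

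The cost is analysis wording. Sera, swabs and serotyping are already planned, and the T0 relation is kept. The price is imprecision in (b), which a pilot of 50 patients cannot avoid.

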**Secondary Outcome Measures:**

- Pneumococcal chemosusceptibility: Number and percentages of antibiotic resistant (including multiresistant) strains
- Molecular epidemiology : Molecular typing combining PFGE (Pulsed Field Gel Electrophoresis), MLST (MultiLocus Sequence Typing) and PCR analysis of bacterial isolates

**STUDY DESIGN**

This is a phase III, prospective, multicenter, pilot controlled study enrolling HIV-infected outpatients, aged 18–65 years with CD4 counts ≥200 cells/µL, pneumococcal vaccine-naïve.

**Study duration: 24 months**

**Phase I:** 12 months(November, 1st 2011 – November, 1st 2012) enrolling + microbiological and serological screening.

**Phase I:** 12 months(November, 1st 2012 – October , 31st 2013) serological and microbliological analyses and data elaboration.

**Inclusion Criteria:**

- > 18 years old
- obtained informed consent
- outpatient
- CD4 ≥200 cells/µl in the last two evaluations before T0

**Exclusion Criteria:**

- > 65 years old
- presence of acute infectious disease
- antibiotic therapy (ongoing or in the previous <= 7 days)
- previous PPV23 or PCV7 vaccination
- Pregnancy
- Current immunomodulatory therapy
- Immunosuppression not HIV related

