**Primary Outcome Measures:**

- Determine the rate of nasal colonization by different pneumococcal serotypes in HIV-positive and HIV-negative adults, in relation to baseline antibody titers at T0;
- Determine the basal serological response (qualitative and quantitative) in HIV-positive and HIV-negative adults;
- Define serological response after one dose of PPV23 vaccine in HIV+ adults;
- Evaluate the effect of one dose of PPV23 vaccine in terms of nasal pneumococcal carriage and occurrence of invasive pneumococcal diseases;

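### The 7-day antibiotic rule covers only the baseline swab, so visit-by-visit before-after carriage comparisons are open to a modest spurious fall

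*Supplement*

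**What the plan says.** The Exclusion Criteria of both protocols rule out "antibiotic therapy (ongoing or in the previous <= 7 days" and also "presence of acute infectious disease". These criteria select patients for entry. In its Sample size and study group selection section, the main study puts it this way: "Applying these criteria, 50 HIV-infected adult outpatients who had never been vaccinated with any pneumococcal vaccine will be prospectively enrolled". The sub-study's corresponding section is built the same way.

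The main study then says "Follow-up visits will be scheduled at 8 (time of second PCV13 dose), 24 and 48 weeks", and at baseline and each visit "nasopharyngeal swabs will be collected, in order to investigate the" presence of *S. pneumoniae*. The sub-study uses the same weeks for its HIV-positive patients. Its HIV-negative subjects have one assessment, at baseline.

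On data capture, the plan says "At baseline and at each visit clinical and anamnestic data from patients will be recorded". Antibiotic use is not named as an item. The Statistic Analysis sections name chi-squared or Fisher tests for proportions, and regression models for colonization and antibiotic resistance without a list of covariates.

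Carriage after vaccination matters in both studies. The main study sets out to "evaluate serological response and prevalence of nasopharyngeal colonization by" *S. pneumoniae* after two doses of PCV13. The sub-study lists among its primary outcomes: "Evaluate the effect of one dose of PPV23 vaccine in terms of nasal pneumococcal carriage".

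**The concern.** The plan controls recent antibiotic exposure on one side of a before-after comparison and not on the other. Every baseline swab comes from a patient who is off antibiotics and has been for more than 7 days. A swab at week 8, 24 or 48 may be taken during or just after a course.

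Detection rests on culture. Swabs are plated on agar, and the PCR described under Analysis of isolates uses DNA from cultured isolates, not from the swab. A carrier whose growth is suppressed is therefore recorded as negative, and no second method would find the organism. The fall this produces in a visit-by-visit comparison has the same sign as a vaccine benefit. No unvaccinated group is followed to show what carriage would have done anyway.

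Antibiotics may also favour resistant survivors, so the secondary outcome on resistant strains could shift among follow-up isolates.

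**Working it through.** The documents state no carriage rate, antibiotic-use rate or power calculation, and they give 50 patients without a derivation. There is no figure of the plan's own to reproduce. What follows is an illustration under stated assumptions.

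**Inputs**
- n = 50 HIV-positive patients in each study (Sample size and study group selection).
- p0, true carriage, the same at all visits because the vaccine is taken to be inert: assumed 5-30%.
- a, share of follow-up swabs taken on or within 7 days of antibiotics: assumed 5-20%. At baseline a = 0, by the exclusion.
- e, share of carriers made culture-negative in those swabs: assumed 50-100%.

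**Step 1: size of the spurious fall.** Expected follow-up carriage is p1 = p0 × (1 − a × e), so the relative fall is a × e, whatever p0 is.
- Low end: 0.05 × 0.50 = 2.5%.
- High end: 0.20 × 1.00 = 20%.
- With 10 carriers among 50: 10 × 0.025 = 0.25 to 10 × 0.20 = 2 carriers lost per visit. Carriage of 20% is shown as 19.5% down to 16.0%.

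**Step 2: chance of a significant fall.** With d = p0 − p1 and n = 50 at each visit, treat the visits as independent, as a chi-squared test does. The approximate chance that a two-sided 5% test shows a significant fall is Φ[(d − 1.96 × se0) / se1], where se0 is the pooled and se1 the unpooled standard error. With no distortion this is 2.5%.

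| p0 | a | e | p1 | Expected carriers of 50 | Chance of a significant fall |
|---|---|---|---|---|---|
| 5% | 5% | 50% | 4.88% | 2.5 → 2.44 | 2.7% |
| 10% | 10% | 90% | 9.1% | 5 → 4.55 | 3.5% |
| 20% | 10% | 90% | 18.2% | 10 → 9.1 | 4.2% |
| 20% | 20% | 100% | 16.0% | 10 → 8 | 7.5% |
| 30% | 20% | 100% | 24.0% | 15 → 12 | 9.9% |

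Last row in full: d = 0.06, pooled proportion 0.27, se0 = √(0.27 × 0.73 × 2/50) = 0.0888, se1 = √((0.30 × 0.70 + 0.24 × 0.76)/50) = 0.0886. Then (0.06 − 0.174)/0.0886 = −1.29, and Φ = 9.9%.

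**Step 3: against sampling error.** With 10 of 50 positive, the exact 95% interval for carriage is 10.0% to 33.7%. The shift at p0 = 20% is 0.5 to 4 percentage points, well inside that interval.

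**Step 4: which comparisons are exposed.**
- Follow-up visit against baseline in the same patients: exposed.
- Follow-up swabs against the baseline-only HIV-negative controls: exposed, if anyone makes that comparison.
- Baseline (T0) comparisons, including HIV-positive against HIV-negative: not affected, because the rule covers both sides.
- PCV13 against PPV23 at the same visit: affected only if antibiotic use differs between the groups.

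**Step 5: after the fix.** Restricting to swabs that meet the 7-day rule makes a = 0 at every visit and a × e = 0, apart from any antibiotic effect lasting beyond 7 days.

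**The case against.** The strongest reply is that this is only missing detail. Clinical and anamnestic data are taken at every visit, they are to be integrated with the microbiology, and multivariate models for colonization and resistance are planned. Recent antibiotic use fits naturally there, since staff must already ask about it at entry. This stands in part, because the data may well be collected. But no 7-day look-back is stated, antibiotic use is not listed as a covariate, and the proportion tests as written set no swab aside.

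A second reply is that the main study's primary carriage outcome is tied to antibody titers at T0, and that its paired test is named for GMCs only. This stands. The point bears chiefly on the sub-study's PPV23 outcome, and in the main study on the broader aim of describing carriage after vaccination.

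A reader might infer something stronger: that every carriage result in both studies is biased in a known direction. The documents do not support that. Clinical follow-up counts a patient as colonized after at least one positive swab. If follow-up swabs are pooled under that definition, three further swabs give more chances to be positive than one baseline swab, which pushes measured carriage up. The acute-infection exclusion also applies at entry only, and nothing in the documents shows which way its absence later would act. The downward direction holds for visit-by-visit comparisons, and for the antibiotic effect alone.

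The size is also wholly assumed and, in a pilot of 50, modest. That stands as well.

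**Conclusion.** The point holds in a limited form. The antibiotic rule protects the baseline swab and no other, so visit-by-visit before-after carriage comparisons are made under unequal conditions, with no followed unvaccinated group to reveal it. Under the assumed ranges the spurious relative fall is 2.5-20%. The chance of a significant fall with an inert vaccine rises from 2.5% to about 10% at the very most, so the harm lies in the estimate more than in false significance. A shift in follow-up resistance percentages is possible but cannot be sized from the documents.

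The conclusion assumes that antibiotics reduce culture detection and that some follow-up swabs fall on or soon after a course. The documents give neither rate. The point is worth correcting because the remedy is cheap, but it does not invalidate either study.

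**What to change.** In both studies, add one form item at weeks 8, 24 and 48: any antibiotic use, ongoing or in the 7 days before the swab. In the Statistic Analysis sections, prespecify that before-after carriage and resistance results are reported twice: once for all swabs, and once restricted to (or adjusted for) swabs that meet the same 7-day rule as baseline.

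Vaccination visits stay as they are. Postponing swabs is less attractive, because the documents define no visit window and week 8 is also the visit for the second PCV13 dose.

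The cost is one question per visit and a sentence or two of analysis text. The restricted analysis loses a few swabs and may introduce some selection, since patients with recent infection are the ones likely to drop out of it. That is the reason to keep the all-swabs result beside it.
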